### Objectives

The primary objective of the HOMEX-SCI study is to assess the impact of a 6-week home-based moderate-intensity arm-crank exercise intervention on markers of metabolic and cardiovascular health in inactive individuals with chronic SCI. Little is known about the impact of a moderate- to vigorous-intensity exercise intervention on messenger ribonucleic acid (mRNA) expression of adipose tissue, which is surprising considering that it is a major site for energy storage. To our knowledge, adipose tissue biology has never been studied in a cohort of individuals with SCI. Thus, a secondary objective is to investigate at baseline, and following intervention, the expression of genes within adipose tissue that are associated with a variety of biological processes such as energy homeostasis, glucose metabolism, lipid metabolism and inflammatory responses. Other objectives include: characterising aspects of adaptive immune function pre and post intervention, quantifying changes in body composition, aerobic capacity, dietary and physical activity behaviours and various constructs of health and wellbeing. The exercise intervention group’s responses, for all outcome measures over 6 weeks, will be compared to a control group.

## Methods

### Study design

This study is a pre-post, parallel-group design, with participants randomly assigned to a 6-week home-based exercise intervention (INT) or a control period (CON). The planned experimental design is summarised below (Fig. 1), consistent with current Consolidated Standards of Reporting Trials (CONSORT) guidelines [60]. The South West (Exeter) National Research Ethics Service Committee has approved this study protocol (REC reference number 14/SW/0106) and the trial has been registered as a current controlled trial (ISRCTN57096451). Upon initial contact (by email or telephone), the study will be described briefly and those interested in enrolling will be asked to read a detailed participant information sheet and complete a health screen questionnaire. Interested individuals will be screened via a telephone conversation 48 hours after their initial contact to ascertain eligibility. A focus will be placed on establishing a good rapport at this initial contact and also as individuals progress through the enrolment process. Written consent will be obtained during the initial laboratory visit and participants will be informed that they can withdraw from the study at any time without consequence.

**Fig. 1 Fig1:**
[figure not shown]
Study flow diagram (Abbreviations: *CON* control group, *INT* exercise intervention group, *PA* physical activity, *PAL* physical activity level, *T2DM* type-2 diabetes mellitus, *V̇O*
_*2*_
*peak* peak oxygen uptake)

Baseline laboratory testing will be performed in the Centre for DisAbility Sport and Health (DASH) at the University of Bath approximately 2 weeks before the INT/CON period commences. During this 2-week interim period participants will be instructed not to alter their normal activity patterns or dietary behaviours. This period permits a 7-day estimation of free-living habitual energy balance, whereby PA is monitored and participants are asked to maintain a detailed weighed record of food intake. The additional time accounts for participants returning the activity monitors, and downloading and subsequent analysis of data to ascertain participant eligibility. A member of the research team will also travel to each participant’s home to deliver a portable arm-crank ergometer and supervise the first exercise session. Importantly, the interim period also allows exactly 8 weeks between baseline and follow-up testing, which ensures that eumenorrheic female participants will be within the follicular phase of their menstrual cycle (3–10 days after the onset of menses) during both laboratory visits. Controlling for menstrual cycle stage is important as hormone fluctuations can influence insulin sensitivity [61].

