#### Power calculation and sample size

The sample size was calculated using statistical software (G*Power 3.1.5) on the main outcome measure, fasting serum insulin concentration. This calculation was based on data from a hand-cycling training group, which reported an improvement of −14.3 ± 12.7 pmol l^−1^ [59] in fasting insulin over 16 weeks. Based upon these data (Cohen’s *d* = −1.1) it was estimated that nine participants are required to detect a statistically significant change in insulin sensitivity in the INT group. The power was 0.8 and the alpha was set at 0.05. As a 2:1 ratio is to be adopted, a computer programme (www.statstodo.com/SSizUnequal_Pgm.php) was used to calculate sample size adjustments for two groups with unequal size, to account for any consequences of unequal allocation on statistical power [99]. Also, taking into account an expected drop-out rate of approximately 15 %, we aim to recruit at least 24 (INT: 16, CON: 8) participants with chronic paraplegia.

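### A fixed 8-week gap does not ensure testing 3–10 days after menses at both visits; control of cycle stage is only partial (minor)

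*Protocol article*

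**What the plan says.** The text after Figure 1 (Study design) places baseline testing "approximately 2 weeks before the INT/CON period commences". The intervention or control period lasts 6 weeks. The article then states that the schedule gives "exactly 8 weeks between baseline and follow-up testing, which ensures that eumenorrheic female participants will be within the follicular phase". The target is spelled out as the "follicular phase of their menstrual cycle (3–10 days after the onset of menses) during both laboratory visits". The reason given is that "Controlling for menstrual cycle stage is important as hormone fluctuations can influence insulin sensitivity".

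The sample size section names the "main outcome measure, fasting serum insulin concentration". The Blood measurements section adds OGTT summaries (iAUC and the Matsuda index) and says that these blood variables, apart from the haematological profile, are assayed in one batch after the last participant finishes.

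The article does not give the number of eumenorrheic women expected or their cycle lengths.

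**The concern.** The article presents the 8-week interval as a mechanism that guarantees a cycle stage at follow-up. Eight weeks is two cycles of 28 days, so the guarantee rests on cycle length, which the article neither restricts nor mentions at this point. A woman tested inside the window at baseline and outside it at follow-up carries a change of cycle stage in her change score. The article itself says that cycle stage can affect insulin sensitivity, and its main outcome is fasting insulin. In a small trial with 2:1 allocation, a few such women need not be spread evenly across the arms. The minimisation factors (age, body mass, lesion level, physical activity level) do not include sex.

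**Working it through.** **Inputs from the article.** Interval between visits: exactly 8 weeks. Lead-in: about 2 weeks. Study period: 6 weeks. Window: 3 to 10 days after onset, which is 8 whole days. Planned sample: 24 (INT 16, CON 8), with about 15% drop-out. Cycle length is not given, so a range is examined as an assumption.

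**The stated interval.** 2 + 6 = 8 weeks = 56 days = 2 × 28. It reproduces if the lead-in is exactly 14 days. If a full 6 weeks follows a lead-in of 13 or 15 days, the gap is 55 or 57 days.

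**Follow-up cycle day.** Let d be the number of days since onset at baseline and S the total length of the two intervening cycles. Then

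follow-up day = d + 56 − S.

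For constant cycle length L, S = 2L, so each day by which L differs from 28 moves the follow-up day by two. A negative result means that the second onset has not yet occurred.

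**Baseline days 3–10 that also give follow-up on days 3–10:**

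| L (days) | Baseline days that work | Count |
|---|---|---|
| 24 | none (follow-up days 11–18) | 0 of 8 |
| 25 | 3–4 | 2 of 8 |
| 26 | 3–6 | 4 of 8 |
| 27 | 3–8 | 6 of 8 |
| 28 | 3–10 | 8 of 8 |
| 29 | 5–10 | 6 of 8 |
| 30 | 7–10 | 4 of 8 |
| 31 | 9–10 | 2 of 8 |
| 32 | none | 0 of 8 |

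Example: for L = 26 and d = 7, follow-up falls on 7 + 56 − 52 = day 11, one day late.

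**How much the window absorbs.** Follow-up is in the window when S lies between d + 46 and d + 53. For d = 6 that is 52–59 days (constant cycles of 26–29 days); for d = 7 it is 53–60 days (27–30 days). All eight baseline days work only when S = 56.

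**Illustration under assumptions.** Assume a mean cycle of 28 or 29 days, a between-woman SD of 0 or 2 days, a within-woman SD of 1 to 3 days, and baseline spread evenly over days 3–10. Simulation then puts about 46% to 86% of follow-up visits in the window. Booking matters: with mean 28, no between-woman variation and a within-woman SD of 1 day, a day-6 baseline stays in the window about 99% of the time and a day-3 baseline about 63%.

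**Scale of the consequence.** After 15% drop-out, about 16 × 0.85 = 13.6 INT and 8 × 0.85 = 6.8 CON participants complete. If one woman's insulin change shifts by x because of cycle stage, her arm's mean moves by about x/14 in INT or x/7 in CON. The article gives no value for x and no count of the women concerned, so the calculation stops there.

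**The case against.** The strongest reply is that only one verb is at fault. The schedule keeps many women in the window, especially with a mid-window baseline, and unequal cycles that total 56 days also work. That stands: a reader might infer that the timing works only for exact 28-day cycles, or that control of cycle stage is not delivered at all, and the table shows neither is so.

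A reader might also infer confounding of the treatment comparison. The document does not support this: both randomised groups follow the same interval, so off-window visits are not tied to allocation by design. Nor can it be assumed that the affected women cluster in the smaller arm; under 2:1 allocation about a third of them would be expected in CON. A visit on day 2 or day 11 is also not shown to be a large hormonal shift.

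The booking remedy has limited reach. The Trial status section reports 21 of 24 recruited by 2 February 2016. With the 56-day gap held, no baseline day works for 24- or 32-day cycles. At L = 31 the usable baseline days put follow-up on days 3–4, at the edge of the window.

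Finally, cycle logging and sensitivity analyses may well be in the full protocol or SAP. Their absence from the article is not criticised here. What remains is that the article states a design property that the schedule does not have.

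**Conclusion.** The statement is wrong as written, and the severity is minor. The calendar arithmetic needs only the article's 56 days and its 3–10-day window: the guarantee holds across the whole window only when two cycles total 56 days, and for constant cycles it falls to 6, 4, 2 and 0 of 8 baseline days as L moves 1, 2, 3 and 4 days from 28. The 46% to 86% range rests on assumed cycle variation.

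The effect is added variability, with possible chance imbalance, in fasting insulin and the OGTT indices among eumenorrheic women. Its size in pmol/l cannot be obtained from the document. No sample size, alpha or power figure changes.

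**What to change.** 1. Say that the 8-week interval *aims to* place both visits in the window, instead of *ensures*.
2. For any participants still to be booked, ask usual cycle length and choose a baseline day d within 3–10 such that d + 56 − 2L is also within 3–10, using the days in the table for L = 25–31. State that this cannot work for 24- or 32-day cycles while the 56-day gap is held.
3. Record the actual cycle day at both visits for every eumenorrheic woman, retrospectively where dates of menses are available.
4. If the SAP does not already do so, prespecify a sensitivity analysis of fasting insulin and the OGTT indices that excludes women outside days 3–10 at either visit. Because insulin is assayed in a single batch at the end, this can be fixed before any insulin result exists.
5. Reconcile the approximate 2-week lead-in with the exact 8-week gap.

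The cost is one screening question, slightly tighter booking for a few women, one extra analysis and two wording changes. For women already tested, items 3 and 4 are the ones that help.

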### Recruitment and randomisation

It has been reported that recruitment for a RCT, especially in the absence of direct access to a clinical population, requires considerably more resources and time than initially anticipated in order to achieve adequate enrolment [62]. In a systematic review, Ross et al., [63] described patient barriers to recruitment for RCTs. These included: (1) additional demands of the trial increasing participant burden and (2) patient preferences for or against a particular treatment. Barriers to research participation are perhaps even more exaggerated for people with disabilities due to complex health problems [64], lack of transportation [65], cognitive impairments and financial stress [66]. With this in mind, we plan to deliver the intervention by setting up arm-crank ergometers in participants’ own homes, thereby minimising any potential accessibility/transport barriers to participants becoming more active. Transportation needs are a major participation barrier for individuals with disabilities, and so travel expenses to the University of Bath for laboratory testing will be reimbursed. Recruitment material will be promoted by nationwide charities and circulated on Internet forums and social networking sites. Previous Centre for DisAbility Sport and Health research participants who met the inclusion criteria of the trial have been notified directly about the study via email.

After baseline laboratory testing and habitual free-living monitoring, the first nine participants will be randomly allocated to the experimental group (INT) or the CON group using a block randomisation plan (fixed block size of nine; allocation ratio of 2:1; no stratification). Randomisation will be performed by an independent researcher using a concealed list generated with a web-based platform (www.randomization.com). Within a highly heterogeneous population such as individuals with SCI, we decided to use minimisation [67] to ensure balance between the two groups for baseline characteristics (age, body mass, level of spinal cord lesion and physical activity level). Subsequent participants who enrol on the trial will, therefore, be allocated to either the INT group or the CON group in order to balance the groups in these variables of interest. We opted for an unequal allocation ratio as it has been supported as an alternative approach for ‘confirmatory trials’ [68, 69], primarily to increase the amount of data on the INT, where individual responses are likely more variable. We presume limited variability in the CON group, as participants will continue to live their normal lifestyle. Any small loss of precision with the use of unequal allocation has been appropriately accounted for in the sample size calculation. While participants may have a strong preference to receive the INT and not be in the CON group, we will try to overcome this by offering a waiting-list control. Participants in the CON group will, therefore, be offered the opportunity to participate in the INT once they have completed the CON period.

### Participants and eligibility criteria

The participants will be inactive individuals (physical activity level; PAL ≤1.60), with a chronic (more than 1 year) spinal cord lesion between the second thoracic and the fifth lumbar vertebrae, who are aged between 18 and 65 years. Volunteers with neurologically incomplete injuries will be considered eligible if they are wheelchair users for more than 75 % of their waking day. Participants will only be included if they have been weight stable (±3 kg) for at least 6 months and have no plans to change their diet or exercise behaviours. Individuals self-reporting active medical issues including pressure sores, urinary tract infections, cardiac disorders, cardiovascular contra-indications for testing [70] or musculoskeletal complaints of the upper extremities will be excluded. Participants on T2DM medication will also be excluded.

Habitual PAL will be estimated over a representative 7-day period following the baseline laboratory visit using a wearable PA-monitoring device (Actiheart™, Cambridge Neurotechnology Ltd., Papworth, UK), which integrates accelerometer and heart rate signals. This device has previously been validated for use in this population [71]. Participants will wear this monitor continuously (24 hours a day) and will be instructed only to remove it when showering or bathing. Individuals with a PAL >1.60 will be precluded from progressing to the group allocation stage.

### Main trial day protocol

The same experimental procedures will be completed on both baseline and follow-up trial days. Participants will arrive at the Centre for DisAbility Sport and Health laboratory at 08.30 ± 1 h, following an overnight fast (at least 10 h). Twenty-four hours prior to each main laboratory trial day, participants will abstain from strenuous exercise, caffeine (tea/coffee) and alcohol. The final exercise bout prescribed in the INT group will be more than 36 h prior to follow-up testing in order to reduce the acute effects from the previous bout of exercise. Participants will also be asked to consume 1 pint of water on the morning of testing to ensure adequate hydration. See Fig. 2 for the schematic overview of the main trial day timeline.

**Fig. 2 Fig2:**
[figure not shown]
Schematic overview of main trial day timeline, with 08.00 arrival time of the participant as an example (Abbreviations: *RMR* resting metabolic rate)

#### Body composition analysis

After being asked to void, body mass will be measured, with participants wearing light clothing, using platform wheelchair scales (Detecto® BRW1000, Webb City, MO, USA). The wheelchair, along with participants’ shoes will be weighed separately and subtracted from the total mass of the participant to derive an accurate body mass as recommended [72]. For body composition analysis, participants will transfer onto a Dual-energy X-ray Absorptiometry (DEXA) scanning table (Discovery, Hologic, Bedford, UK). Supine height will be measured in centimetres along the left hand side of the body using a non-elastic tape measure (Lufkin, Sparks, MD, US). Participants will be positioned centrally on the scanning table with their feet spaced evenly either side of the mid-point of the body, with their arms placed mid-prone with an equal gap to the trunk on both sides. For participants who experience leg spasms, their knees will be flexed at a 45°-angle and supported by a pillow. Participants will be instructed to remain as still as possible. All scans will be conducted following a daily QC scan of a Spine Phantom as per the manufacturer’s instructions.

#### Resting metabolic rate measurement

Resting metabolic rate (RMR) will be estimated by indirect calorimetry from expired air samples collected into 200-L Douglas Bags (Hans Rudolph, Kansas City, MO, USA) via falconia tubing (Baxter, Woodhouse and Taylor Ltd., Macclesfield, UK) with concurrent measurement of inspired air composition; a reliance of standard atmospheric concentrations has recently been discouraged [73]. The process of indirect calorimetry has previously been described in detail [74]. Expired concentrations of oxygen (O_2_) and carbon dioxide (CO_2_) will be measured, from a known volume of each sample using paramagnetic and infrared analysers, respectively (MiniMP 5200, Servomex Ltd., Sussex, UK). Four 5-min Douglas Bag samples will be collected for RMR in accordance with best practice guidelines [75]. Measurements will be conducted following a 20-min rest and ambient laboratory temperature will be maintained between 20 and 25 °C. RMR will be taken as the average of two or more Douglas Bag samples that are within 100 kcal day^−1^ of each other. Participants will also wear a Polar T31 heart rate monitor (Polar Electro Inc., Lake Success, NY, USA) during RMR measurement; resting heart rate values will be averaged over the 20-min collection period.

#### Blood sampling

After a 15-min supine rest, a cannula (BD Venflon Pro, BD, Helsingborg, Sweden) will be inserted into an antecubital vein, and a 45-ml fasting sample drawn. From this sample, 25 ml of whole blood will be collected into sodium heparin tubes and peripheral blood mononuclear cells (PBMCs) will be isolated using density gradient centrifugation using standard methods. Cells in freezing medium (70 % Roswell Park Memorial Institute (RPMI) media, 20 % fetal bovine serum (FBS), 10 % dimethylsulphoxide (DMSO)) will be frozen at −1 °C/min using a Nalgene ‘[name] container. Samples will be stored at −80 °C and assayed for immunological measurements within 12 months.

The remaining blood from the baseline sample (and subsequent blood samples during the oral glucose tolerance test; see oral glucose tolerance test section below) will divided into separate tubes for obtaining serum and plasma. For serum, whole blood will be placed into a serum separation tube and left to stand at room temperature for 15 min before centrifugation. For plasma, whole blood will be placed into tubes coated with ethylenediaminetetraacetic acid (EDTA) and centrifuged immediately. Samples will be centrifuged (Heraeus Biofuge Primo R, Kendro Laboratory Products Plc., Tyne and Wear, UK) at 5000 rpm for 10 min at 4 °C, with serum/plasma subsequently dispensed into 0.5-ml aliquots and immediately cooled on dry ice and then stored at −80 °C. A small aliquot of EDTA blood will be used to obtain the full leucocyte differential and other haematological variables (SF-300, Sysmex Ltd., Milton Keynes, UK).

#### Adipose tissue biopsy

An adipose tissue sample will be collected from the area around the waist, approximately 5 cm lateral to the umbilicus, using a well-established ‘needle aspiration’ technique [76]. The area will be thoroughly disinfected with Videne, before injection of anaesthetic (approximately 5 ml lignocaine hydrochloride 1 %) into a small area. Five minutes later, a needle will be inserted in the subcutaneous fat tissue around the waist in order to collect approximately 1–2 g of fat tissue. Swabs and pressure will be applied to the area once the sample has been collected. A dressing will then be applied to the area. The sample will be cleaned with isotonic saline and any clots will be manually removed. After the sample has been weighed, it will be homogenized in 5 ml of Trizol (Invitrogen, Paisley, UK) and stored at −80 °C.

#### Oral glucose tolerance test (OGTT)

After the baseline blood sample and adipose tissue biopsy, the participant will consume 113 ml of Polycal (Polycal, Nutricia Advanced Medical Nutrition, Trowbridge, UK) and 87 ml of water, equivalent to 75 g of anhydrous glucose, within 5 minutes. Further 5-ml blood samples will be drawn at 15-min intervals for the next 2 hours. The intravenous cannula is to be kept patent through periodic flushing with 0.9 % NaCl (B. Braun, Sheffield, UK) infusion, with the first 5 ml of each blood draw being discarded. Blood pressure will also be measured during the final 15 min of the OGTT using an automated blood pressure monitor (Boso Medicus Prestige, Bosch + Sohn GmbH, Jungingen, Germany). The short form-36 health survey (SF-36), the EuroQol-5 dimensions, 5 levels questionnaire (EQ-5D-5 L), the Wheelchair User’s Shoulder Pain Index (WUSPI), the Fatigue Severity Scale (FSS) and the Exercise Self-efficacy Scale (ESES) will be administered during the last 30 min of the OGTT.

#### Exercise testing pre and post intervention

Participants will undertake an incremental submaximal arm-crank ergometry test using a portable desktop ergometer (Monark compact rehab 871E, Dalarna, Sweden). This test will comprise three 3-min stages, separated by a 1-min rest period during which the resistance will be increased. Participants will be instructed to maintain a cadence of 75 rpm throughout. A variety of power outputs will be chosen that are sufficient to cover the relative exercise intensities (60–65 % of V̇O_2_ peak) employed during training sessions in the INT group. During the final minute of each stage, V̇O_2_ and heart rate will be recorded to determine the relationships between V̇O_2,_ exercise intensity (work rate) and heart rate. This test will be performed on the same ergometer provided to each participant during the INT.

Peak oxygen uptake (V̇O_2_ peak) will be determined at the end of each laboratory visit using a continuous, progressive intensity test on an electrically braked arm-crank ergometer (Lode Angio, Groningen, Netherlands). A cadence of 75 rpm will be encouraged throughout and a starting intensity will be selected based on the participant’s training history. The resistance will be increased by 14 W every 3 minutes until the point of volitional exhaustion (approximately 9–12 min). Continuous gas exchange measurements will be collected using a TrueOne® 2400 computerized metabolic system (ParvoMedics, Salt Lake City, UT, USA), calibrated according to manufacturer’s instructions prior to use.

